### Randomisation

Patients included in the study will be randomly allocated to one of the two groups. One group will undergo a clinical and functional rehabilitation programme, and the other group will be considered a control, without exercise intervention.

The allocation list will be concealed from all outcome assessors. In order to balance the groups in terms of number of participants, as well as between men and women, a 1:1 block randomisation will be used, stratified by sex. The randomisation process will be carried out using an online software *www.randomizer.org*. This stage will be performed by a researcher who will not be involved in the other experimental procedures of the study.

After baseline evaluations of each patient block, one manager of the study will send the code identifiers of the patients for randomisation by e-mail. This same manager receives by e-mail the allocation list and informs the exercise training providers, while the other manager, responsible for the contact with patients, informs the patients individually about allocation and corresponding procedures (starting training or control procedure meeting).

### Functional capacity

The assessments of functional capacity will be performed at baseline, at week 12 and after 24 weeks of intervention. The functional indicator of cardiorespiratory fitness and the primary outcome of the study will be evaluated by the 6-min walk test, following the protocol of the American Thoracic Society [13], which consists of measuring the total walking distance in a predetermined area of 30 m long during 6 min. During the test, the patient will be encouraged by the evaluator through standardised incentive phrases, every minute respectively: “There are 5 min left to finish the test. Keep the pace”; “There are 4 min left to finish the test. Keep the pace”; “You’ve already taken half the test. Keep the pace”; “One min. to finish the test. Keep the pace”; and finally, when the timer reaches zero or reaches 6 min, “Stop”. Every 2 min, during the patient’s walking, the values of the distance covered, HR, SpO_2_, dyspnea effort and RPE will be recorded. The test will be stopped immediately if the patient reports chest pain, intolerable dyspnea, leg cramps, staggering gait, diaphoresis and a pale or grey appearance, or if there is a decrease in SpO_2_ of more than 4%. If the test is stopped for any of these reasons, the patient should be seated or lie supine. After the test is properly completed, the number of laps completed will be recorded as well as the total distance covered, blood pressure (systolic and diastolic), O_2_ saturation, heart rate, dyspnea effort (Borg Scale CR-10) and lower limbs (LL) effort (Borg Scale CR-10). The referred physiological and effort measures will be evaluated also in the first, second, third and sixth minute of recovery. After 15 to 20 min of recovery, the test is performed again, following the same protocol, adopting the better score as the final outcome.

Functional mobility (dynamic balance and agility) will be evaluated by the Timed-Up-and-Go (TUG) test. The TUG will follow the following protocol: from a sitting position in a chair (with back supported), the subjects will get up from it (without the help of hands), walk and go around a Chinese demarcation plate positioned on the ground 3 m away and will sit again (with their backs supported). Two attempts will be made at each of the speeds: maximum (TUG-m) and usual (TUG-h), with a 1-min interval between each attempt, with the shortest time for each speed being recorded [25].

The muscular aerobic capacity of the lower limbs will be evaluated by a sit and stand test of 30 s, following the battery protocol of Rikli and Jones (2013) [26], measuring the number of repetitions performed. Flexibility will be evaluated by the sit and reach test, using the Wells bench, by following protocol: participants should sit facing the referred instrument with their knees fully extended and jointed, placing one hand on the other, leaning the trunk forward and reaching as far as possible with the fingertips on the ruler, not being allowed to flex the knees. Each participant will have two attempts, and the highest value achieved will be recorded. Four different scales involving functional status will be applied, which are as follows:Post-Covid-19 Functional Status (PCFS), Portuguese version, is an ordinal scale, containing six response levels, comprising the full range of functional outcomes, focusing on limitations of tasks and activities of daily living, both at home, work/study, as well as lifestyle changes [27].Modified Medical Research Council (MMRC) consists only of a question about shortness of breath at different levels of activity, being scored from 0 (best clinical condition) to 4 (worst clinical condition) [28].Tilburg Frailty Indicator is a multidimensional assessment questionnaire for frailty in the elderly, consisting of 15 questions, distributed in physical, psychological and social domains [29].Sarcopenia Form (SARC-F) involves five questions about strength components, need for assistance when walking, getting up and sitting in a chair, climbing stairs and history of falls. The scoring scale has three levels from 0 to 2 points for each item, with the total scoring range being between 0 and 10 [30].Chalder Fatigue Scale consists of seven questions addressing physical fatigue and four questions addressing mental fatigue. The answers should be understood by the frequency of occurrence (never, rarely, sometimes and always) [18].Post-Exertion Malaise Scale addresses five questions about the individual’s sensations in relation to physical exertion. Questions should be answered regarding the frequency (never, a little, half the time, most of the time, always) and the severity (absent, mild, moderate, severe, very severe) in which they occur [31].The Patient-Specific Functional Scale (PSFS) was developed especially for patients with musculoskeletal disorders. It consists of an interview in which the patient chooses five important activities whose execution is difficult or impossible due to his disability or health problem. For each activity, the patient assigns a difficulty score from 0 (“unable to perform the activity”) to 10 (“able to perform the activity at the same level as before the injury or problem”). In subsequent reassessments, the patient re-scores the initial activities or identifies new activity limitations that have arisen over time [32].

### Neuromuscular outcomes

Isometric handgrip strength will be measured using the Carci^@^ handgrip dynamometer (CEFISE, São Paulo, SP) at baseline and after 24 weeks of intervention. Three measurements will be performed on each hand, with a 1-min interval among them, the highest value being recorded.

To assess the isometric force production capacity from the elbow and knee flexor and extensor muscle groups, a micro FET2 HHD manual dynamometer (Hoggan Health Industries, Salt Lake City, Utah) will be used. For the measurement, it will be necessary for the participant to exert force against the dynamometer that indicates the result of the force produced in newtons (N). The maximum isometric contraction values will be recorded. Measurements will be made on the three muscle groups bilaterally, and the highest value of three contractions will be recorded. An interval rest of 1 min will be applied between each contraction in order to avoid muscle fatigue.

To determine the 90° angle of the position of the elbow, knee and hip joints, a universal goniometer with two 20-cm-long rods and a fulcrum with a measurement precision of 2° (*Trident Gon-pvc*) will be used. The sitting position will be adopted for knee assessment, and the lying position will be adopted for the elbow and hip assessment. The individual being evaluated will sit on a stretcher, on which their feet will not touch the floor.

### Anthropometry and body composition assessments

Anthropometric and body composition measurements will be performed at baseline, at the 12th week and after 24 weeks of intervention. Such measurements will always be carried out in the morning on an empty stomach (at least 4 h of fasting). All participants will be instructed not to perform physical exercise the day before data collection and to abstain from alcoholic, caffeinated and other diuretic beverages in the 48 h preceding the test. Participants will be instructed to wear gym clothes, without zippers or metal, to be barefoot, without earrings or rings or any type of metal, and urinate 30 min before the assessment [33]. In addition, the participants will be asked to inform researchers about the use of a cardiac pacemaker or bone prosthesis, and the use of diuretic or calcium-related drug. After completing the assessments, participants will receive a snack, which will consist of a package of highly nutritious cookies (25 g) and a banana.

The body mass (multifrequency Bioimpedance InBody® 720 model, Biospace, Los Angeles, USA) and height (Stadiometer, Alturaexata®, with 1 mm precision) will be recorded and their data will be used to determine the body mass index (BMI). Waist circumference will be measured (flexible and inelastic measuring tape, Cescorf®, with a precision of 1 mm) and with it, the waist-to-height ratio will also be determined.

Computed densitometry by dual energy radiological absorptiometry (DXA), Hologic®, Discovery WI Fan-beam model - S/N 81593 (Hologic Inc., Bedford, Massachusetts, EUA) will be used to assess fat mass, fat-free mass, lean mass, bone mineral density and visceral adipose tissue, expressed in absolute and relative terms. The device will be calibrated before the analyses and will be used following the manufacturer’s recommendations. The assessment will be done in automatic and whole-body mode.

The phase angle (PhA) will be estimated using a multifrequency Bioimpedance InBody® 720 model (Biospace, Los Angeles, USA), with eight electrodes, measuring resistance at five frequencies (1, 50, 250, 500 and 1000 kHz) and reactance in three (5, 50 and 250 kHz). To estimate the PhA, the raw values of the BIA will be used: resistance (R) and reactance (Xc). The technique provides impedance (Z) and Xc data at a frequency of 50 kHz, and from these, the R value will be calculated by the proportional sum of the body, in which the upper limbs represent 40% of the total body R, the trunk represents 10% and the lower limbs represent 50%. Thus, the PhA, expressed in degrees (°), will be calculated through the equation: PhA = Arctangent (Xc / R) × (180°/ π) [34]. The device will be calibrated and used according to the manufacturer’ recommendations. In addition, from Bioimpedance, data on total body water (intra- and extracellular) and basal metabolic rate are also obtained.

### Respiratory outcomes

Respiratory outcomes will be assessed at baseline and after 24 weeks of intervention. Pulmonary function assessment will be performed following the procedures recommended by the American Respiratory Society (ATS) and the European Respiratory Society (ERS) for the respiratory oscillometry [35], spirometry (slow manoeuvre) [36] and single-breath carbon monoxide uptake in the lung (https://erj.ersjournals.com/content/49/1/1600016). The equipment will be calibrated daily before carrying out the assessments with a 3-L syringe according to the specifications of the manufacturers [37].

Respiratory system impedance (Zrs), resistance of respiratory system at 5 Hz (Rrs5), reactance of respiratory system at 5 Hz (Xrs5) and area of reactance (AX), in kPa/L/s, will be measured before and after the administration of the bronchodilator salbutamol (400 μg) using the impulse oscillometry system (IOS) MasterScreen JAEGER™ (Germany) [36]. The ratio between inspired volume and vital capacity (VI/VC) in %, diffusing capacity of the lungs for carbon monoxide (DLCO) in mL/min/mmHg, alveolar volume (VA) in L and transfer coefficient of the lung for carbon monoxide (KCO) in mL/min/mmHg/L will be measured using the Vmax® VIASYS Respiratory Care Inc (USA). The values of DLCO, VA and KCO will also be calculated in % predicted [38].

### Cardiovascular outcomes

Clinical blood pressure, heart rate variability and vascular function will be assessed, all at rest, at baseline, at week 12 and after 24 weeks of intervention. Blood pressure measurements at rest will be performed on two non-consecutive days, using automatic blood pressure monitoring equipment (OMRON, model HEM-7113, Brazil), with cuffs appropriate to the circumferences of the participants’ arms, following the recommendations of the Brazilian Guidelines on Hypertension [39]. Therefore, on each of the 2 days, the participants will remain at rest, sitting in a calm environment for 10 min, and then three measurements will be performed, with a 1-min interval between them. For analysis purposes, the average of all measurements performed on each measurement day will be adopted.

Heart rate variability (HRV) will be measured by collecting R-R intervals, beat-to-beat, using a Polar heart rate monitor, Vantage V2 model. Participants must remain at rest in a supine position for 10 min, and later the recording of R-R intervals will be performed for another 10 min. This data will initially be exported to the Polar Flow programme from the Polar Flow Sync software.

Subsequently, the data will be filtered to eliminate possible noise from ectopic beats or device reading errors in the order of 20 bpm [40], and the percentage of correction of the R-R intervals cannot exceed 2%. This procedure will be performed in Polar Precision Performance software, version 4.03. In the decomposition of the parameters provided by the HRV, the respective R-R intervals will be exported to the HRV Analysis Software – Kubios programme (The Biomedical Signal Analysis Group, University of Kuopio, Finland) and the analyses will be performed in the time and frequency domains. In the analysis of the frequency domain, the Fourier transform is used to quantify the low-frequency (LF: 0.04–0.15 Hz) and high-frequency (HF: 0.15–0.4 Hz) bands, in units normalised, following the recommendations of the Task Force of the European Society of Cardiology and the North American Society of Pacing and Electrophysiology [41].

Prior to blood pressure and HRV collections, patients will receive the following instructions: 24 h without practising moderate or vigorous physical activity; 12 h without ingesting alcoholic beverages, teas, coffee, coca cola, or any beverage or food containing caffeine; take medication as usual (if in the morning, take it before coming in; if at night, take it the night before); maintain light and usual food the day before and on the day of collection. In addition, on collection days, it will be recommended that the patient empty their bladder immediately prior to assessment, if necessary.

Vascular function will be assessed using the flow-mediated dilation (FMD) technique using the LOGIQ S7 Expert Ultrasound device (GE Healthcare), following the recommendations of Thijssen [42]. Before the start of collection, individuals will receive the following guidelines: (a) rest in a quiet and dark room for a period of 10 to 15 min, (b) avoid exercise for at least 24 h, (c) avoid alcohol and foods or beverages that contain caffeine or are rich in polyphenols for at least 12 h and (d) maintain a light and habitual diet the day before and on the day of collection.

Individuals will remain lying down in dorsal decubitus, with the arm extended at heart level for the evaluation of FMD. The measurement will be performed in the brachial artery on the right side. At that moment, a cuff will be placed on the subject’s forearm, 5 cm from the antecubital fossa. The ultrasound should be adjusted for vascular analysis of the brachial artery. The transducer will be positioned over the brachial artery, seeking to obtain the best possible image in B-mode. From there, the ultrasound parameters must be configured so that the image is obtained with optimal quality. Then, the Doppler function will be activated to capture the blood flow together with the image of the artery in real time.

For the collection of the FMD, the diameter and the blood flow of the artery baseline will be evaluated before the inflation of the cuff, for a period of at least 30 s. The cuff will then be inflated to 50 mmHg above the individual’s systolic BP for 5 min, after which the cuff will be deflated, and diameter and blood flow measurements will be evaluated for 3 min. Post-deflation diameter measurement will begin 30 s prior to cuff release. Blood velocity will be assessed using an insonation of 60° or less. During the entire collection, continuous measurements of the flow velocity and the diameter of the brachial artery, through the Doppler function, will be recorded for future analyses. Pre- and post-intervention assessments will be standardised and performed at similar times of day.

Data analysis will be performed using continuous edge detection and wall-tracking software, and automated mathematical algorithms will be used to calculate peak diameter. The baseline diameter and the FMD response in absolute (mm) and relative (%) changes will be presented.

### Cardiorespiratory fitness

A maximal incremental cycle ergometer test (Lode Excalibur Sport, Lode BC, Groningen, Netherlands) will be performed at baseline and after 24 weeks of intervention. The initial workload will be 20 W maintained during 4 min, followed by 10 W increments every 30 s until voluntary exhaustion. Participants will be instructed to maintain cadence at 65–75 rpm throughout the test. The test will end when the cadence drops more than 10 rpm for more than 5 s. The VO_2_ will be measured breath by breath throughout the procedure from the expired gas (COSMED, model QUARK PFT ERGO, Rome, Italy), with subsequent reduction of the data to averages of 15 s. The VO_2_ peak will be considered as the highest value obtained during the test in the 15-s intervals. The QUARK PFT ERGO system will be calibrated before each test to ensure accurate measurements of ambient air, cylinder gas, turbine and delay, in accordance with the manufacturer’s recommendations. The peak power (PP) will be considered the highest workload reached during the test.

HR monitoring will be performed by means of an HR monitor incorporated into the gas analyser, allowing the recording and storage of HR behaviour synchronised with VO_2_. To consider the tests as maximum, the criteria proposed by Basset and Howley [43] will be adopted. The ventilatory threshold (LV1) will be determined as follows: (a) the moment in which a first non-linear increase in the carbon dioxide production ratio will occur (VCO_2_) versus VO_2_ (v-slope method); (b) an increase in minute ventilation (VE) relative to VO_2_ (VE/VO_2_) without an evident increase in VE/VCO_2_; and (c) a first increase in the final tension of O_2_ without a drop in the final tension of CO_2_ [44]. The second ventilatory threshold (LV2) will be determined by the increase in minute ventilation (VE) relative to VCO_2_ (VE/VCO_2_) without an evident increase in VE/VO_2_ [45].

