### Secondary outcomes

As secondary outcomes, indicators of functional capacity, neuromuscular parameters, anthropometrical and body composition, respiratory, cardiovascular, cardiorespiratory, behavioural and psychosocial parameters will be evaluated.

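### As written, the rule for the second ventilatory threshold (LV2) can be met only if VCO2/VO2 falls, whereas the LV1 rule in the same section needs that ratio to be rising; one secondary parameter is affected

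*Protocol article*

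**What the plan says.** All the relevant text is in the protocol article, under Cardiorespiratory fitness, except where another section is named.

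- **Test.** A maximal cycle test starts at 20 W, "followed by 10 W increments every 30 s until voluntary exhaustion". It "will be performed at baseline and after 24 weeks of intervention". Gas exchange is measured breath by breath and reduced to 15-s averages.
- **LV1, criterion (a).** "the moment in which a first non-linear increase in the carbon dioxide production ratio will occur (VCO_2_) versus VO_2_ (v-slope method").
- **LV1, criterion (b).** "an increase in minute ventilation (VE) relative to VO_2_ (VE/VO_2_) without an evident increase in VE/VCO_2".
- **LV1, criterion (c).** This uses end-tidal gas tensions and plays no part in the argument.
- **LV2.** There is one criterion, with a literature citation: "the increase in minute ventilation (VE) relative to VCO_2_ (VE/VCO_2_) without an evident increase in VE/VO_2".
- **Status.** Secondary outcomes lists the domain only in general terms: "respiratory, cardiovascular, cardiorespiratory, behavioural and psychosocial parameters will be evaluated". LV2 is not named there. The primary outcome is the 6-min walk distance.

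**The concern.** The LV2 sentence is LV1 criterion (b) with the two ventilatory equivalents exchanged. The exchange looks symmetrical, but the two ratios are not free to move independently: they differ by the factor VCO2/VO2. The LV1 pattern needs that factor to rise. The LV2 pattern needs it to fall, at a higher load in the same test.

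An assessor who follows the sentence literally would either find no LV2 in a technically sound test or accept a point where noise in the 15-s averages makes the ratio dip. Apart from the word second, nothing in the sentence requires the point to lie above LV1. At stake is whether LV2 can be reported at all, and whether a reader could tell how it was scored. The multiple imputation in the Analysis plan could not restore a variable that has no valid observed values.

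**Working it through.** The plan states no figure on this point, so there is nothing to reproduce. The check is algebra on the section's own definitions, followed by illustrations with assumed values.

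**1. Identity.** Write R = VCO2/VO2. Then VE/VO2 = (VE/VCO2) × R. If VE/VCO2 changes by a fraction a and R by a fraction b, VE/VO2 changes by (1 + a)(1 + b) − 1.

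**2. What the LV2 rule needs.** It needs a > 0 and (1 + a)(1 + b) − 1 ≤ 0, that is b ≤ 1/(1 + a) − 1, which is negative. So R must fall.

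**3. What the LV1 rule needs.** Criterion (b) has VE/VO2 rising with VE/VCO2 not evidently rising. With a near 0, the change in VE/VO2 is about b, so b > 0 and R is rising at LV1.

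Criterion (a) does not by itself prove this. The v-slope break says that the slope dVCO2/dVO2 increases. Since dR/dVO2 = (slope − R)/VO2, R rises only once the slope exceeds the current R. The argument therefore rests on criterion (b).

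**4. Size of the conflict.**

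| Rise in VE/VCO2 | VE/VO2, R flat | VE/VO2, R +2% | VE/VO2, R +5% | Change in R for flat VE/VO2 |
|---|---|---|---|---|
| 5% | +5.0% | +7.1% | +10.3% | −4.8% |
| 10% | +10.0% | +12.2% | +15.5% | −9.1% |

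For example, 1.05 × 1.05 − 1 = 0.1025, and 1/1.05 − 1 = −0.048.

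**5. Worked example (assumed values).** At the onset of LV2, let VE/VCO2 = 28 and R = 1.05, so VE/VO2 = 28 × 1.05 = 29.4. A minute later, let VE/VCO2 = 30 and R = 1.10, so VE/VO2 = 30 × 1.10 = 33.0. VE/VCO2 has risen by 30/28 − 1 = 7.1% and VE/VO2 by 33.0/29.4 − 1 = 12.2%. To keep VE/VO2 at 29.4, R would have to drop from 1.05 to 29.4/30 = 0.98 while the load is increasing.

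**6. Simulated test (assumed values).** The VCO2–VO2 slope is 0.85 before LV1 and 1.05, 1.2 or 1.4 after it. The VE–VCO2 slope steepens at LV2 by a factor of 1.2, 1.5 or 2.0. In all nine combinations:

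- R rose throughout after LV1.
- From LV2 to the end of the test, VE/VCO2 rose by 1.9% to 21.1% and VE/VO2 by 5.0% to 30.1%, always the larger of the two.
- The written LV2 condition was met at 0 of the 80 grid points where VE/VCO2 was rising. With the VE/VO2 condition dropped, all 80 qualify.

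The simulation has a rising R built in. It illustrates step 2 and is not independent evidence.

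**The case against.** **The consequence depends on literal use.** The sentence cites a method source that is not available here, and the Outcomes section says that experienced researchers make the assessments. Because the rule is unworkable, an assessor would probably notice at the first test, so a slip in the writing is at least as plausible as a faulty working rule. This stands. Nothing in the document shows that any test was scored by the literal wording, and the consequence has to be stated conditionally.

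**The wording may allow latitude.** The qualifier evident does not help, because with R flat or rising the relative rise in VE/VO2 is at least as large as the rise in VE/VCO2 that the assessor must see. The intent may have been no new breakpoint in a VE/VO2 that is already climbing. The sentence does not say so, and if that was meant it still needs correcting.

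**The article is condensed.** That excuses omissions. This is a complete criterion, stated wrongly.

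**Stronger readings the documents do not support.** A reader might infer selective missing data or a biased treatment comparison. A rule that fails in every valid test loses LV2 for everyone, which is not selective. If LV2 is placed at noise points, assessors are blinded and the same rule applies in both arms at both visits, so the direct expectation is added measurement error; no mechanism for a difference between arms appears. A reader might also infer that the trial can no longer show effects on cardiorespiratory fitness. VO2 peak, peak power and LV1 have their own definitions and are untouched.

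**Conclusion.** The LV2 rule is wrong as written. It requires VCO2/VO2 to fall, while LV1 criterion (b) requires the same ratio to be rising from LV1 in a test that continues to exhaustion. The algebra is certain and needs no outside source. That the ratio does not turn down again in a valid test at higher load is an inference from the section's own description of LV1 and the rising workload; the document does not state it separately.

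If the sentence is applied literally, this one secondary cardiorespiratory parameter is lost or made noisy at baseline and week 24. How many values would be affected cannot be estimated from the document. The primary outcome, the sample size, the primary analysis, VO2 peak, peak power and LV1 are unaffected, and no between-arm bias is shown. It is a definite but contained error in an outcome-scoring rule, and it should be corrected.

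**What to change.** In Cardiorespiratory fitness:

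- Delete the closing condition on VE/VO2 from the LV2 sentence.
- Define LV2 as the point above LV1 at which VE/VCO2 begins a sustained rise, with VE/VO2 continuing to rise.
- Re-read from the stored gas-exchange data, blinded to arm and by the corrected rule, any LV2 scored under the current wording. If assessors already used another rule, state that rule in place of the current sentence.

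The cost is one sentence, plus the re-reading if any scoring was done. No new tests are needed, provided that the gas-exchange files have been kept.
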